## Abstract

**Introduction:**

First-time traumatic anterior shoulder dislocation (TASD) is predominantly managed non-operatively. People sustaining TASD have ongoing pain, disability and future risk of redislocation. There are no published randomised controlled trials (RCTs) comparing different non-operative rehabilitation strategies to ascertain the optimum clinically effective approach after TASD.

**Methods and analysis:**

In this multicentre adaptive RCT, with internal pilot, adults with a radiologically confirmed first time TASD treated non-surgically will be screened at a minimum of 30 sites. People with neurovascular complications, bilateral dislocations or are unable to attend physiotherapy will be excluded.

Randomisation will be on a 1:1 treatment allocation, stratified by age, hand dominance and site. Participants will receive a single session of advice; or a single session of advice plus offer of further physiotherapy (maximum 4 months). The primary analysis will be the difference in Oxford Shoulder Instability Score at 6 months. A sample size of a minimum of 478 participants will allow us to show a four point difference with 90% power.

An embedded qualitative study will explore the participants’ experiences of the trial interventions.

**Ethics, registration and dissemination:**

Funded by NIHR HTA (16/167/56), 1 June 2018; National Research Ethic Committee approved (18/WA/0236), 26 July 2018. First site opened 5 November 2018 and final results will be updated on trial registries and submitted to a peer-reviewed journal and will inform rehabilitation strategies after a TASD. Study Within A Trial (SWAT) funded by MRC (MR/R013748/1), 1 May 2019; registered on the MRC-HTMR All-Ireland Hub (reference number SWAT 121).

**Trial registration number:**

ISRCTN63184243. (Trial stage: Pre-results)

Strengths and limitations of this studyUK-wide trial across a minimum of 30 sites to optimise external validity.Primary outcome measure is patient centred.The main limitation is that the intervention could not be blinded.

## Introduction

The shoulder is the most frequently dislocated joint; occurring in 8.2–23.9 per 100 000 people per year.^1^ Traumatic anterior shoulder dislocations (TASDs) occur when excessive forces during a traumatic event displace the humeral head frontwards, out of the shoulder socket, resulting in the joint surfaces completely losing contact.^1–3^ They predominantly occur in men under 25 years during high-impact events and women over 80 years during low-impact events.^1^

People sustaining TASD often have ongoing pain, disability and morbidity linked to redislocation and subsequent need for repeated management.^1–3^ Rehabilitation may reduce these events and restore a functional, painless shoulder through restoration of movement and retraining muscles.^2^ However, a Cochrane review has found no evidence to support this^2^; Dutch national guidelines explicitly do not refer to physiotherapy^3^ and UK guidelines cite referral *‘*may be helpful’.^1^

This research protocol will investigate the hypothesis regarding the nature and extent of what physiotherapy is required for the management of patients following TASD with an embedded ‘Study Within A Trial (SWAT)’ to compare two strategies for retention of participants in randomised controlled trial (RCTs).

## Research questions

### RCT research question

In adults with first time TASD managed non-operatively does a single session of advice and course of physiotherapy improve the Oxford Shoulder Instability Score (OSIS) by a minimum of four additional points at 6 months when compared with a single session of advice only?

### SWAT research question

Does making a courtesy introductory telephone call to recruited participants improve response rates to 6 months follow-up questionnaires compared with a written card with similar information?

## Objectives

### RCT primary objective

To quantify and draw inferences on observed differences in the OSIS score between a single session of advice and physiotherapy with a single session of advice only, for adults with first time TASD managed non-operatively, 6 months postrandomisation.

### RCT secondary objectives

To estimate comparative cost-effectiveness (cost/quality-adjusted life-years, QALY) of the two trial treatments, from an National Health Service (NHS) and personal social services perspective.To determine the difference in complication rate (eg, shoulder redislocation) in the first 12 months between the trial treatment groups.To quantify and draw inferences between the functional status (OSIS) of the trial treatment groups at 6 weeks, 3 and 12 months.To quantify and draw inferences on observed differences in the functional status (Disabilities of the Arm, Shoulder and Hand) of between the trial treatment groups at 6 weeks, 3, 6 and 12 months.To quantify and draw inferences on observed differences of health-related quality of life (EQ-5D-5L) between the trial treatment groups at 6 weeks, 3, 6 and 12 months.To qualitatively explore participants’ experiences of receiving the trial treatments and identify facilitators and obstacles to adhering to them.

### SWAT primary objective

Evaluate the impact of making a courtesy call to newly recruited participants in the Acute Rehabilitation following Traumatic anterior shoulder dISlocAtioN (ARTISAN) trial on response rates to 6 months follow-up questionnaires compared with a written card with similar information.

### SWAT secondary objectives

Time to response to the questionnaires at each time points.Response rates at 6 weeks, 3, 6 and 12 months.Completeness of responses.Number of reminder notices required.Cost of intervention per participant.

## Methods and analysis

### Study design

Multicentre, adaptive, RCT with internal pilot and SWAT.

### Outcome measures

Outcome measures will be collected at baseline (prerandomisation) at the recruiting site and then at 6 weeks, 3, 6 and 12 months centrally from Warwick Clinical Trials Unit (WCTU) by postal questionnaire, mobile application, telephone or email.

#### RCT primary outcome

OSIS: Self-completed outcome measure containing 12 questions (0–4 points each), with possible scores from 0 (best function) to 48 (worst function).^4 5^ Questions relate to activities of daily living particularly relevant to patients exhibiting shoulder instability and has been designed to assess outcome of therapy.

#### RCT secondary outcomes

##### Disabilities of the Arm, Shoulder and Hand

Self-completed shortened version of the Disabilities of the Arm, Shoulder and Hand (QuickDASH) questionnaire. Uses 11 items to measure physical function and symptoms in people with any or multiple musculoskeletal disorders of the upper limb. Designed to help describe the disability experienced by people with upper-limb disorders and monitor changes in symptoms and function over time.^6^

##### EQ-5D-5L

Health-related quality of life measure consisting of five dimensions, each with 5 levels of response. Each combination of answers is converted into a health utility score. Gives a single preference based index value for health status that can be used for broader cost-effectiveness comparative purposes.^7^

Complications: Complications will be defined into three categories:

Predefined complications directly related to the interventions.Predefined complications directly caused by the primary TASD event not identified by the initial assessing clinician, but subsequently identified.Complications not related to the intervention or TASD event and will subsequently not be formally analysed or reported.

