### Randomisation

#### RCT randomisation

Participants will be randomised at the end of the initial advice session via a web-based system. Allocation concealment will be maintained by an independent randomisation team at WCTU, who will be responsible for generation of the sequence and will have no role in the allocation of participants. The treatment group will be allocated by computer using a minimisation algorithm with a random element and stratification by participant age (39 years old and under and 40 years old and over), hand dominance and recruiting site.

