### Interventions

#### RCT interventions

The interventions will be reported in line with the template for intervention description and replication (TIDIER) and Consensus on Exercise Reporting Template (CERT) checklists.^10 11^ All participating centres will receive an initial training session from the trial team. Following this, a lead physiotherapist at each site will be identified to complete subsequent training of additional physiotherapists. This training will be supported with web-based materials and a trial intervention manual.

All participants will receive a period of initial immobilisation in internal rotation as per UK national guidelines, for a duration of up to 2 weeks from date of injury.^1^ At this time participants will be provided with a web-link to phase 1 of the ARTISAN advice materials and provided with a paper-based booklet version covering:

What has happened to me?What can go wrong?How do I stop this happening again?How long do I have to wear my sling?Should I move my arm?How do I control my pain?When can I return to usual activities?What if something goes wrong?

All participants will subsequently receive an appointment for a physiotherapy advice session within 6 weeks of injury. At the first appointment, all participants will receive a single session of advice to aid self-management, lasting up to 1 hour and administered by an ARTISAN trained physiotherapist. Following routine assessment, the physiotherapist will deliver the above core set of intervention components and in addition:

Points of contact if complications occur or expected recovery times are not achieved.A core set of progressive phase 2 range of movement exercises and what they aim to achieve.Enhancing self-management behaviours through the addition of goal setting, exercise planning and diaries.

The physiotherapist will provide details of web-based materials, which will include all the core components above in written and video format, and will include a dedicated area for participants to set goals and keep diaries. The physiotherapist will also inform the participants that the website resources contain phase 3 progressive strengthening exercises and what they aim to achieve and later stage phase 4 progression to aid return to sports. Participants will be offered paper-based alternatives.

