### Adverse event management

Serious adverse events (SAEs) will be entered onto the SAE reporting form and reported to the central study team. SAEs that may be expected will be predefined and recorded on the participant’s follow-up questionnaire. SAEs that may be expected as part of a TASD are: damage to nerve or blood vessels, fractures, redislocation, torn ligaments or muscles, persistent exacerbation of shoulder pain, restriction of range of movement, adhesive capsulitis (frozen shoulder) and persistent instability. All SAEs will be reported to the sponsor (Warwick University and University Hospitals Coventry and Warwickshire), ethics committee and oversight committees.

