To address the possibility that these might exist, a single interim analysis is preplanned to re-estimate the sample size. This will occur after approximately 200 participants have completed the 3 months follow-up questionnaire, while recruitment is still open. The pooled SD of the primary outcome and presence of therapist effects will be estimated by calculating the therapist intraclass correlation coefficient and its 95% CI. Models will not include treatment effects. A revised sample size calculation will be discussed with DMC and TSC and if appropriate, permission requested from the funder to adjust the sample size.

All primary analyses are planned to be on an intention-to-treat basis with secondary per protocol analyses. The main analysis will investigate differences in the primary outcome measure, 6 months after randomisation, between the two treatment groups. Unadjusted and adjusted regression analyses will be used to estimate the between group difference. The adjusted analyses will adjust for the stratification variables, baseline scores and any other clinically important variables. Since individual clinicians will treat only a small number of participants enrolled in the trial, we do not expect clinician-specific effects to be important in this study.

Descriptive statistics of functional outcome data (ie, QuickDash and EQ-5D-5L) at each time point will be constructed with between group analyses following the method set out for the primary analysis above. Patterns of recovery will also be explored. Secondary analyses will includeχ^2^ tests to compare the number of dislocations and other complications between allocation groups. For important complications (eg, dislocations), Kaplan-Meier curves of the time to complication will be constructed. If sufficiently large numbers of complication groups are observed, Cox regression models will be constructed to compare the time to complication in each arm. Temporal effects will be investigated using a multilevel model of all follow-up data.

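### The complication outcome is sorted by judged cause: a new redislocation does not fit the categories, injuries that predate randomisation count as outcomes, and events judged unrelated go unanalysed and unreported

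*Protocol article*

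**What the plan says.** RCT secondary objectives: "To determine the difference in complication rate (eg, shoulder redislocation) in the first 12 months between the trial treatment groups".

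RCT secondary outcomes, in the complications paragraph printed under the EQ-5D-5L heading, sorts complications into three categories:

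1. "Predefined complications directly related to the interventions"
2. "Predefined complications directly caused by the primary TASD event not identified by the initial assessing clinician, but subsequently identified"
3. "Complications not related to the intervention or TASD event and will subsequently not be formally analysed or reported"

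RCT statistical analysis plans chi-squared "tests to compare the number of dislocations and other complications between allocation groups", Kaplan-Meier curves for important complications with dislocation as the example, and Cox models if numbers allow. It does not refer to the three categories.

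Adverse event management lists redislocation among the SAEs that may be expected as part of a traumatic anterior shoulder dislocation (TASD). It has predefined expected events recorded on the follow-up questionnaire, and states that "All SAEs will be reported to the sponsor" and to the ethics and oversight committees.

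On timing: "All participants will subsequently receive an appointment for a physiotherapy advice session within 6 weeks of injury", and "Participants will be randomised at the end of the initial advice session via a web-based system". The Blinding section says that neither participants nor treating clinicians are blind, and that follow-up is run centrally without the treating clinicians.

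**The concern.** A randomised comparison of complications is protected when each arm counts the same kind of event, arising after randomisation, whatever anyone thinks caused it. The three categories depart from this in three ways.

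- **The named event has no clear place.** The categories do not describe a new redislocation during follow-up, so two people applying them could file it differently.
- **Some outcomes are older than the allocation.** Category 2 injuries date from the index event. Allocation can affect only whether they are found, and one arm is offered further physiotherapy sessions for up to 4 months.
- **Whether an event counts depends on a post-randomisation judgement.** Category 3 events leave both analysis and report once judged unrelated, in a trial where participants and treating clinicians know the allocation.

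At stake is how the complication objective, the only secondary objective on harm, is read. The primary outcome is not affected.

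**Working it through.** **The plan's own figure.** No number is stated for complications. The only planned size is 478, for the primary outcome: difference 4, SD 12, two-sided 5% (assumed), 90% power. The t-test calculation gives 191 per arm; 191 / 0.8 = 238.75, rounded up to 239; 2 × 239 = 478. The figure reproduces. It supplies the 191 followed up per arm used below and has no other bearing on this point.

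**Step 1: put a new redislocation through the categories.**

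| Category | Does a new redislocation fit? |
|---|---|
| 1, directly related to the interventions | Not necessarily, least of all after a single advice session |
| 2, index-event injury missed at first assessment | No. It is a new event, not a missed old one |
| 3, related to neither | Hard to square with Adverse event management, which ties redislocation to the TASD |

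The objectives and the analysis section both require it to be analysed. The intention is plain; the category wording does not deliver it.

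**Step 2: timing of category 2.** The order is index injury, then advice session (within 6 weeks of injury), then randomisation, then follow-up. A category 2 injury occurs at the first of these. Its true frequency is balanced by randomisation in expectation, so with equal detection it adds noise and not bias.

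*Illustration; all rates are assumptions.* Redislocation 20% in one arm and 10% in the other, with a proportion c having a category 2 event independently in both arms. Combined proportion = 1 − (1 − p)(1 − c). Power is by the two-proportion normal approximation, 191 per arm.

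| c | Combined proportions | Risk ratio | Power |
|---|---|---|---|
| 0 | 20% v 10% | 0.50 | 78% |
| 5% | 24% v 14.5% | 0.60 | 66% |
| 10% | 28% v 19% | 0.68 | 55% |
| 20% | 36% v 28% | 0.78 | 39% |

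*Unequal detection (assumed).* Suppose 10% in each arm have such an injury, found in 80% of the physiotherapy arm and 50% of the advice arm. Category 2 then contributes 10% × 0.8 = 8% against 10% × 0.5 = 5%, a 3-point excess with no true difference. Added without overlap to an equal 8% redislocation rate, this gives 16% v 13%, which would reach p<0.05 in that direction about 13% of the time.

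**Step 3: category 3.** Suppose true rates are equal, but 10% of events in one arm and 30% in the other are judged unrelated and dropped (assumed). The analysed proportions are p × 0.9 and p × 0.7.

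| True rate | Analysed | Chance of p<0.05 in that direction |
|---|---|---|
| 10% | 9% v 7% | about 11% |
| 15% | 13.5% v 10.5% | about 15% |
| 20% | 18% v 14% | about 19% |

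With no distortion the chance in one direction would be 2.5%. These figures show that the mechanism can matter. They do not show that it will operate.

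**The case against.** Much of the case against stands.

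- **Redislocation is not lost.** A reader might infer that it falls into category 3 and goes unanalysed. The documents do not support that. Adverse event management links it to the TASD, the objectives name it, and the analysis section tests and plots it. What remains is a misfit between sections.
- **Pooling is not stated.** The analysis section specifies no composite of category 2 events with redislocation. However, only category 3 is excluded from formal analysis, so category 2 is by implication compared between arms in some form.
- **The detection rates are invented, and ascertainment is partly protected.** Questionnaires go to both arms at the same time points, follow-up is central, and advice-arm participants with continuing problems are directed to the clinic or their general practitioner. A reader might infer that the safety conclusion would point the wrong way. The documents give no rates from which to say so. Unequal detection remains possible because contact differs by design.
- **Category 3 does not hide serious events.** All SAEs go to the sponsor and committees. That does not put them in the trial's comparison or report. Who assigns relatedness is a detail an article may leave to the full protocol, so biased attribution is a risk and not a demonstrated fault. The rule itself is stated, not left out.
- **The chi-squared wording.** A reader might infer that repeat dislocations would be counted as separate events. The phrase is loose, and its natural reading is participants with or without an event.
- **Onset also needs judgement.** Dating a tear or nerve injury found late is not free of opinion. This limits the fix without removing its advantage for redislocation.

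**Conclusion.** The point holds as a weakness in how a secondary outcome is defined. Three things follow from the text without assumed rates: the categories do not accommodate a new redislocation that other sections treat as central; category 2 counts injuries that allocation cannot have caused; and category 3 removes events from analysis and reporting on a judgement made after randomisation in an open-label trial.

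The size of any effect is unknown. Dilution follows if category 2 events are included in a comparison. Bias requires, in addition, unequal detection or unequal attribution, neither of which the documents establish. The change is worth making because it removes a post-randomisation judgement from a named secondary objective at little cost.

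**What to change.** Reconcile the complications paragraph with the objectives, Adverse event management and RCT statistical analysis, and define the outcome as follows.

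1. Compare by arm the participants with at least one redislocation after randomisation, regardless of judged cause.
2. Separately, compare by arm the participants with at least one other predefined shoulder complication first arising after randomisation, regardless of judged cause.
3. Report index-event injuries identified late in their own table, by arm and descriptively only.
4. Tabulate by arm the recorded complications judged unrelated, and all SAEs, in place of leaving them unreported. Attribution can be shown as a description but should not decide inclusion.

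**Cost.** Rewording and a few extra table rows. Expected events are already captured on the follow-up questionnaires and SAEs on their own form. The article does not say that non-serious unrelated events are collected, so item 4 covers only what is recorded. Onset date will still need some judgement for injuries found late.

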##### Resource use questionnaires

Primary health economic analysis will concentrate on direct intervention and healthcare/personal social services costs, while wider impact (societal) costs will be included within the sensitivity analyses.

##### Embedded qualitative interviews

A purposive sample, up to 50 participants, informed by treatment allocation, gender, age and outcome will be invited for one interview, to explore the participant experience of receiving the interventions and facilitators and obstacles to adhering to them.

#### SWAT primary outcome

Response rate: Proportion of participants who return the questionnaire.

#### SWAT secondary outcomes

Time to response: Date of first sending questionnaire to date of questionnaire received by study team.

Completeness of responses: Number of missing items per questionnaire.

Number of reminder notices: Number of notices administered by the trial team.

Cost of intervention: Cost of phone call or postcard per participant.

### Sample size

#### RCT sample size

A worthwhile difference from this intervention is four points on the OSIS.^8 9^ The SD of the OSIS 6 months after injury is 10 points.^8 9^ However, the literature has predominantly included a young population, given that we will recruit a wider range of ages a larger SD is expected, therefore an SD of 12 is more likely. To show a four-point difference at 5% significance level with 90% power allowing a margin of 20% loss during the follow-up needs a minimum of 478 participants.^5 9^

